**Figure 2 F2:**
[figure not shown]
Follow up of patients.

### Blood pressure and pulse measurement

All Blood Pressure (BP) measurements taken by the Physician will be performed in a standardised way using digital blood pressure equipments (Model M5, Omron) supplied and validated for the study. BP will be measured on the right upper arm in the sitting position, after a rest of 5 minutes. Using an appropriate sized cuff (which will be recorded) connected to a digital device, and the same arm (which will be recorded), at a similar time of day (which will be recorded), two measurements will be taken at a minute interval. Instructions will be given to the Physicians to ensure that the lower edge of the bladder be placed 2-3 cm above the position of maximal pulsation of the brachial artery in the arm, just above the antecubital fossa. Care would be taken to ensure that the cuff fits firmly, comfortably and is well secured. The mean of the two readings will be used for analysis.

Pulse measurements will be recorded by the digital blood pressure equipment (Model M5, Omron), after a rest of 5 minutes. The digital BP equipment records the systolic, diastolic BP and the pulse in the same sitting, which would be recorded. The average of the two readings will be used for the analysis.

### Height, weight and waist circumference measurements

The participants would be weighed in light indoor clothing with a digital weighing machine (Tanita weighing Scale) with 100 g accuracy, which would be standardized across all the centers. Height would be measured in bare feet with Seca 213 Portable Freestanding stadiometer, accurate to 1 mm. Care would be taken to ensure that all the PHCs have the same equipment make, type and validation procedures.

### Data collection

Data on known cardiovascular risk factors (age, sex, tobacco usage, history of diabetes mellitus, family history of premature coronary artery disease); any associated clinical conditions (physician certified cerebro vascular disease, cardiovascular disease, renal, vascular diseases); target organ damage (physician certified left ventricular hypertrophy, hypertensive retinopathy and microalbuminuria); and quality of life scores (based on WHO BREF questionnaire will be collected at 0, 6 and 12 months after randomization.

### Quality of life questionnaire

World Health Organization (WHO) QoL BREF questionnaires, which have been validated in Indian settings for chronic diseases, would be utilised in this study. WHOQOL was designed as an international cross-culturally comparable quality of life assessment instrument [17]. This 26-item questionnaire has been tested and validated in Hindi language [17], and tested in Indian patients suffering from chronic diseases [18-20]. The questionnaire would be translated into the local language (Telugu) and back translated by two independent translators. A third reviewer would compare the translated and back translated versions. The finalised questionnaire will be field tested in 10% of the proposed sample size for cultural appropriateness. Questions which are deemed to hurt the cultural sensitivity would be modified based on pilot test results. This modified questionnaire will then be applied to the study. Patients would be asked to read and answer the questions on their own. In case of linguistic or other difficulties, the questionnaire would be administered by interview.

### Cost effectiveness analysis

A comparison of costs in monetary units with outcomes in quantitative non-monetary units would done in the Cost Effectiveness Analysis (CEA) [21]. Resources required for intervention and values attached to those resources and effects of treatment (either benefit or harm) and values attached to those effects for the both the groups will be compared to determine the cost effectiveness ratios. Cost effectiveness ratios, that is the cost/outcome of different interventions, enable opportunity costs of each intervention to be compared.

#### Perspective

A third party payer perspective will be employed in this project, as this would enable the tangible costs to be directly compared between both the intervention arms.

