#### Costs

The value of all goods, services, and other resources consumed in providing health care or dealing with side effects or other current and future consequences of health care comprise the direct costs. Direct health care and direct non health costs will be measured in this study. The physician services, hospital services, drugs, costs of the DSS software development, costs for charts (posters) etc. involved in delivery of health care would comprise the direct health care costs. Transportation to and from the site of care would comprise the indirect costs. Marginal costs analysis would be done in which how outcomes change with changes in costs (e.g., relative to a comparator), would be analysed. The time horizon for the costs involved would be for a duration of a year.

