#### Outcomes

A reduction or worsening of systolic BP would be compared (in non monetary terms). The time horizon would be for a duration of one year.

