#### Discounting

Thus, costs and outcomes will be *discounted* relative to their present value (e.g., at a rate of three - five percent per year) so as to account for the effect of time on the value of the outcomes and costs, as they may have less value in the future. Opportunity costs, which would be reflected by discounting, would also be calculated.

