#### Sensitivity analysis

Since any estimation of costs and outcomes has an uncertainty element attached to it, a sensitivity analysis, which would include a change in discount rates, would be done to account for the changes in the cost-effectiveness planes of one intervention compared to another.

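### The economic analysis declares a third-party payer perspective, but its only named non-health cost is transport, which is labelled indirect and not said to be reimbursed by a payer

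*Protocol article*

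**What the plan says.** All of this is in the protocol article.

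- **Perspective:** "A third party payer perspective will be employed in this project". The payer is not identified.
- **Costs, categories:** "Direct health care and direct non health costs will be measured in this study".
- **Costs, transport:** "Transportation to and from the site of care would comprise the indirect costs". No other non-health item is named.
- **Costs, software:** "costs of the DSS software development, costs for charts (posters) etc. involved in delivery of health care would comprise the direct health care costs". No amount, useful life or allocation rule follows.
- **Costs and Outcomes, horizon:** "The time horizon for the costs involved would be for a duration of a year" and "The time horizon would be for a duration of one year".
- **Discounting:** costs and outcomes are discounted "at a rate of three - five percent per year".
- **Sensitivity analysis:** "a sensitivity analysis, which would include a change in discount rates, would be done". No other parameter is named.
- **Cost Effectiveness Ratio and Cost utility analysis:** both ratios have the between-arm cost difference as numerator, and neither section says which cost items enter it.
- **Conclusion:** wider use of the system after this study is envisaged.

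**The concern.** The perspective decides which costs count. Under a payer perspective a cost counts only if the payer bears it. Travel to an outpatient clinic is normally paid by the patient, so it belongs to a patient or societal analysis unless the payer reimburses it. Here it is listed among the costs of a payer analysis, with a label that does not match the categories announced just before it.

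Two of the three secondary end points, cost effectiveness and cost utility, rest on this numerator, and the Abstract offers the results to policy makers. If the cost items are not settled in advance, two analysts could follow the same text and report different ratios.

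The software cost raises a second, smaller question. It is incurred once, in one arm, for a tool that the authors expect to use beyond the trial. How much of it one year should carry is a choice that the text leaves open, and the one sensitivity parameter that is named does not examine it.

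**Working it through.** The protocol gives no cost, no ICER and no software life, so there is no stated figure to reproduce. The first step compares the text; the other steps are illustrations.

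**1. Perspective against cost list.** Three readings of the Costs section are possible.

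| Reading | Consequence |
|---|---|
| Transport is the announced direct non-health cost | It is measured, conflicts with a payer perspective, and the indirect label is wrong |
| Transport really is indirect | It is outside the categories said to be measured, and the direct non-health category has no named content |
| The payer reimburses transport | The perspective would fit, but no section says so and the label still conflicts with the categories |

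None of them reconciles the sections as written.

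**2. How far transport could move the ratios.** Physical measurements and questionnaires are scheduled at 0, 6 and 12 months without distinction by arm. Lifestyle advice is given at 0, 6 and 12 months in the decision support arm and at 0 months in the chart arm, but these times coincide with the common measurement times. With equal numbers of scheduled trips, transport largely cancels in a cost difference. What remains would come from unscheduled visits or from differences in cost per trip, and the document gives no figure for either.

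**3. Share of software cost falling in one year.** Inputs: r = 3% and 5% (Discounting); useful life L = 3 and 5 years (my assumption, not in the document). The share of a one-off cost carried by one year is

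share = r / (1 − (1 + r)^−L)

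| L (assumed) | r = 3% | r = 5% |
|---|---|---|
| 3 years | 0.03 / (1 − 1.03^−3) = 0.3535 | 0.05 / (1 − 1.05^−3) = 0.3672 |
| 5 years | 0.03 / (1 − 1.03^−5) = 0.2184 | 0.05 / (1 − 1.05^−5) = 0.2310 |

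So one year carries about 35–37% or 22–23% of the development cost, against 100% if it is fully expensed. For this one component, expensing is 2.7 to 2.8 times (L = 3) or 4.3 to 4.6 times (L = 5) the annuitised amount.

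**4. What the named sensitivity analysis can show.** Over one year, a cost falling at month 12 is multiplied by 1/1.03 = 0.971 or 1/1.05 = 0.952. Moving between the two rates changes it by 1 − 1.03/1.05 = 1.9%. Costs incurred earlier change by less. Varying the discount rate in this way says almost nothing about how the software cost should be allocated.

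**The case against.** The case against has four parts.

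- **Transport may not be in the numerator at all.** Read literally, only direct costs are measured and transport is called indirect. The document also does not say that patients pay for it. Both statements are correct. But this reading leaves the announced direct non-health category empty, so the contradiction moves rather than disappears.
- **The effect is small.** Scheduled travel largely cancels between arms and the primary blood pressure comparison is untouched. This stands, and it limits the point to a minor one.
- **A one-year horizon can properly include a start-up cost.** This also stands. A reader might infer that the whole development cost is charged to the trial year, spread over the 800 patients of the decision support arm, and that the analysis is therefore biased against the system. The document does not say this: it lists the cost as a category and sets a horizon, with no allocation rule. Nor is it a fault that the cost falls on one arm, since a cost that exists only because of the system belongs to that arm in an incremental analysis.
- **Allocation rules may sit in a fuller economic plan, and the sensitivity wording does not exclude other scenarios.** Fair. The absence of an annuitisation rule is therefore not an error in itself. The extra scenario is worth naming because the authors envisage scale-up and the one parameter they name cannot address it.

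**Conclusion.** The point holds for the perspective. The Perspective and Costs sections do not agree, and the Costs section contradicts itself on how transport is classified. The numerator shared by the cost-effectiveness ratio and the ICER is therefore not coherently defined. That travel is paid by patients is an inference from usual practice; the document offers no statement to the contrary.

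For software development, only an addition is warranted. The allocation choice could change that single component about 2.7- to 4.6-fold, given assumed lives of 3 to 5 years and the protocol's 3–5% rate. The effect on the ICER cannot be computed. No mismatch with the one-year horizon and no definite bias against the decision support system should be claimed.

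Severity is minor: secondary end points only, correctable by wording and one added scenario.

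**What to change.** 1. Keep the base case strictly to the payer and name the payer. Exclude transport unless the plan states that the payer reimburses it.
2. Report transport in a separate patient or societal analysis, classified as a direct non-health cost, and correct the indirect label.
3. Report the ICER twice: with software development fully expensed in the year, and with it annuitised over a stated useful life that is varied (for example 3 and 5 years, at 3% and 5%).

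This needs revised wording and additional cost scenarios, but no new data. The small drawback is that a useful life must be assumed, which is why it should be varied.

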#### Costs

The value of all goods, services, and other resources consumed in providing health care or dealing with side effects or other current and future consequences of health care comprise the direct costs. Direct health care and direct non health costs will be measured in this study. The physician services, hospital services, drugs, costs of the DSS software development, costs for charts (posters) etc. involved in delivery of health care would comprise the direct health care costs. Transportation to and from the site of care would comprise the indirect costs. Marginal costs analysis would be done in which how outcomes change with changes in costs (e.g., relative to a comparator), would be analysed. The time horizon for the costs involved would be for a duration of a year.

#### Outcomes

A reduction or worsening of systolic BP would be compared (in non monetary terms). The time horizon would be for a duration of one year.

#### Discounting

Thus, costs and outcomes will be *discounted* relative to their present value (e.g., at a rate of three - five percent per year) so as to account for the effect of time on the value of the outcomes and costs, as they may have less value in the future. Opportunity costs, which would be reflected by discounting, would also be calculated.

#### Sensitivity analysis

Since any estimation of costs and outcomes has an uncertainty element attached to it, a sensitivity analysis, which would include a change in discount rates, would be done to account for the changes in the cost-effectiveness planes of one intervention compared to another.

#### Cost Effectiveness Ratio (CER)

The costs and outcomes for both the outcomes will be calculated to yield a CER.

(1)$$\text{CER}=\{\left(\text{Cost of DSS}–\text{Cost of chart based}\right)/(\text{Primary outcome of DSS}–\text{primary outcome of chart based intervention})\}$$

### Cost utility analysis (CUA)

Measures costs in monetary units with outcomes in terms of their utility attribute [Quality Adjusted Life Years (QALYs)], i.e. cost per QALY. Cost utility would be measured by Incremental Cost Effectiveness Ratios (ICERs) between both the groups. ICER is a ratio between the differences in the cost involved between the intervention proposed (in Indian National Rupees) and the difference in QALYs between the groups.

Health Related Quality of Life (HRQoL) would be measured on a Visual Analogue Scale (VAS) preference scale with a maximum score of 100 (perfect or best imaginable health) and minimum score of 0 (a quality of life which equals worst health imagined) to measure the value of the health state. The weights for the quality will be based on the (1) preferences of the participants, (2) measured on an interval scale and (3) anchored on perfect health and death. The value of a health state would then be combined with the time spent to calculate the total QALYs. Usefulness, interpretability, and responsiveness were the determining factors to choose VAS as the preferred way to measure the utility of the present health state.

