#### Sample size, sampling and recruitment

Table 1 gives the details of the sample size calculations. To detect a difference of 4 mm Hg Systolic Blood Pressure (SBP), the individual randomization sample size has been calculated at 239 subjects per intervention arm (SD of 19.5 mm for SBP [22]), with a 80% power and an alpha of 0.05. Since, cluster randomization is being attempted in this study, the individual randomization sample size has to be adjusted by a design effect of 2.98 [design effect = 1+ (size of cluster -1) * Intra cluster Correlation (ICC)]. The ICC for the clusters among the Mahabubnagar district, AP, India (study site) has been calculated to be 0.02 (based on the Indian sentinel surveillance study done on a representative sample from 10 sites in India). Hence, the cluster adjusted sample size is 713 hypertensive patients (8 clusters with 125 subjects in each cluster to allow for a 20% loss to follow up) per intervention arm to detect a 4 mm Hg difference in Systolic Blood Pressure (SBP) with a power of 80% and an alpha of 0.05. After adjusting for the coefficient of variation among the various clusters (CV = 0.25), the sample size per intervention arm is 741, i.e. a total of 8 clusters (with equal cluster size of 100 each) would be required per intervention arm.

**Table 1 T1:** sample size calculations

**Detectable difference in SBP between both the groups**	**80% power with an ICC of 0.02**				**90% power with an ICC of 0.02**			
	**Sample size required for individual randomization per arm**	**Sample size required for cluster randomization per arm (DE = 2.98)**	**Sample size required for cluster randomization with CV = 0.25 (DE = 3.1)**	**Minimum no of clusters with a cluster size of 100**	**Sample size required for individual randomization per arm**	**Sample size required for cluster randomization per arm (DE = 2.98)**	**Sample size required for cluster randomization with CV = 0.25 (DE = 3.1)**	**Minimum no of clusters with a cluster size of 100**
4 mm of Hg	374	1115	1160	24	500	1490	1550	32
5 mm of Hg	**239**	**713**	**741**	**16**	320	954	992	20
6 mm of Hg	166	495	515	12	222	622	689	14

*ICC* = Intra Cluster correlation; *DE* = design effect; *CV* = coefficient of variation.

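### The only cost-utility measure named is the ICER; a negative value is ambiguous and, with 8 PHCs per arm, an unadjusted QALY difference is noisier than it need be

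*Protocol article*

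**What the plan says.** Cost utility is a declared secondary end point and part of the stated objective. The section on cost utility analysis says "Cost utility would be measured by Incremental Cost Effectiveness Ratios (ICERs) between both the groups" and gives the formula: "ICER is a ratio between the differences in the cost involved between the intervention proposed (in Indian National Rupees) and the difference in QALYs". Utility "would be measured on a Visual Analogue Scale (VAS) preference scale with a maximum score of 100", and "The value of a health state would then be combined with the time spent to calculate the total QALYs". On costs, "The time horizon for the costs involved would be for a duration of a year".

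Uncertainty is mentioned in the sensitivity analysis part of the cost-effectiveness section: "a sensitivity analysis, which would include a change in discount rates, would be done to account for the changes in the cost-effectiveness planes". The sample size section states that "8 clusters (with equal cluster size of 100 each) would be required per intervention arm".

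The article gives no SD or ICC for the VAS, no expected QALY gain and no VAS visit schedule. The schedule of 0, 6 and 12 months in the data collection section refers to the WHO BREF questionnaire. The text neither specifies nor excludes adjustment of the QALY difference for baseline.

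**The concern.** Two features of the chosen measure matter.

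First, a ratio of two differences loses information. Its sign does not show which arm is better, and it is unbounded as the QALY difference approaches zero. This follows from the formula and needs no assumption about the data.

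Second, a one-year QALY is value multiplied by time. If the VAS is taken at month 0, the starting value is part of each patient's QALY. If it is not, later values are still likely to correlate with starting health. Either way, a chance difference in starting health between two sets of 8 PHCs passes into an unadjusted QALY difference. Randomisation makes this variance, not bias, but the variance falls on the denominator of the ratio.

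At stake is whether the result meant to inform policy makers can be read at all, and whether it is as precise as the data allow.

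**Working it through.** **The plan's own figure.** There is none for the VAS, QALYs or the ICER, so nothing can be reproduced. The number and size of clusters and the SBP design effect come from the article; the rest is assumed.

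**Sign of the ratio.** Let C and Q be positive amounts.
- DSS cheaper and better: ICER = (-C)/(+Q) = -C/Q.
- DSS dearer and worse: ICER = (+C)/(-Q) = -C/Q.

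The same number supports opposite decisions. Incremental net benefit at threshold λ, that is λ × QALY difference minus cost difference, gives λQ + C in the first case and -(λQ + C) in the second.

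**Discount-rate sensitivity.** This is the only variation that the article names. Over one year, moving from 3% to 5% changes a value by at most 1.05/1.03 - 1 = about 2%. If costs and outcomes are discounted alike, it cancels in the ratio. It does not address sampling error in the denominator.

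**Inputs for the QALY difference.**
- From the article: 8 PHCs of 100 per arm, so 800 per arm; ICC 0.02 and design effect 1 + 99 × 0.02 = 2.98, both stated for SBP.
- Assumed: the same ICC for the VAS; VAS SD 0.15-0.20 on a 0-1 scale; VAS at 0, 6 and 12 months; correlation 0.5 between any two visits, at patient and PHC level alike; true gains as tabulated.

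**Standard errors.**
1. Difference at one visit: SD × √(2 × 2.98/800) = 0.0129 (SD 0.15) to 0.0173 (SD 0.20).
2. Area under the curve with weights 1/4, 1/2, 1/4: the squared weights sum to 0.375 and the cross-products to 0.625. Unadjusted variance factor: 0.375 + 0.5 × 0.625 = 0.6875.
3. Covariance of the QALY with the month-0 value: 0.25 + 0.5 × 0.75 = 0.625. Adjusted variance factor: 0.6875 - 0.625² = 0.297.
4. Unadjusted SE: √0.6875 × (0.0129 to 0.0173) = 0.011 to 0.014. Adjusted SE: √0.297 × (0.0129 to 0.0173) = 0.007 to 0.009.
5. SE ratio: √(0.297/0.6875) = 0.66, a cut of about a third. It is 0.72 at correlation 0.4 and 0.51 at correlation 0.7.

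**Chance of a wrong-signed denominator**, Φ(-gain/SE):

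| True gain (QALY) | Unadjusted | Adjusted |
|---|---|---|
| 0.005 | 32-36% | 24-30% |
| 0.01 | 18-24% | 8-14% |
| 0.02 | 3-8% | 0.2-1.7% |
| 0.03 | 0.3-1.8% | below 0.1% |

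**Wider range.** A second set of assumptions took SD 0.10-0.20, ICC 0.01-0.10, visit correlation 0.5 within patients and 0.8 between PHC means. The unadjusted (adjusted) chance is then 5-37% (0.1-23%) at 0.01, 0.1-26% (0-7%) at 0.02 and 0-16% (0-1%) at 0.03. At SD 0.15 and ICC 0.02 it is 20% (4%) at 0.01, 4% (about 0%) at 0.02 and 0.5% (about 0%) at 0.03, and adjustment roughly halves the SE (0.0117 to 0.0058).

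Neither calculation credits the matching of PHCs or their selection within revenue divisions, and neither charges for degrees of freedom lost with 16 clusters.

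**The case against.** The strongest reply is that the formula is simply the textbook definition of an ICER. It says what is compared, not how the difference is estimated, and a baseline-adjusted, cluster-aware QALY difference satisfies it equally well. A condensed article normally leaves adjustment and intervals to an analysis plan. This stands. A reader might infer that the plan commits to an unadjusted analysis, but the text does not say so, and its silence is not an error.

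Three further inferences go too far.
- That the denominator will easily change sign: this holds only for gains of about 0.01 QALY or less under the main assumptions, and the article gives no expected gain.
- That baseline imbalance alone would produce a wrong sign: 8-14% remains after adjustment at a gain of 0.01, so much of the risk is ordinary sampling error. Chance imbalance does not bias the estimate.
- That the ratio would be presented with nothing else: the article does refer to cost-effectiveness planes, and a plane separates dominant from dominated. That reference sits in the cost-effectiveness part, however, and names only discount rates.

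PHCs are also matched on population size and literacy and drawn from four revenue divisions, which may reduce imbalance by an amount the article does not quantify. Finally, the ICER is a conventional summary, and preferring net benefit is partly a matter of reporting. The reply does not remove the ambiguity of a negative ratio, or the fact that no other cost-utility measure is named.

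**Conclusion.** The point holds as a worthwhile improvement to the stated measure, not as proof of a defective analysis. The ambiguity of a negative ICER and its instability near a zero denominator follow from the formula alone. The precision argument is conditional: under the main assumptions adjustment reduces the SE by about a third, equivalent to 1/0.657² = about 2.3 times the sample. The sign of the denominator is fragile at a gain of 0.01 QALY or below and largely secure at 0.03, unless the VAS ICC is well above the 0.02 borrowed from SBP. All VAS inputs, including measurement at month 0, are assumptions. The primary SBP comparison is not affected.

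**What to change.** In the cost utility section of the article's underlying protocol, or in the health-economic analysis plan:
- Estimate the QALY difference adjusted for month-0 VAS, with PHC as the cluster. State when the VAS is taken. If it is not taken at month 0, adjust for the month-0 WHO BREF score, which is already collected; the gain in precision then depends on how well that score predicts the later VAS.
- Report the cost difference, the QALY difference and incremental net benefit over a stated range of rupee thresholds alongside the ICER, with intervals from a method that respects PHC clustering.
- Where one arm dominates, say so in words instead of quoting a negative ICER.

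This changes wording and analysis only and needs no further patients or measurements. The cost is that a threshold range must be named and justified in advance.

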#### Secondary end point

· To compare the Quality of Life (QoL) scores at 0 and 12 months among hypertensive patients randomized to receive the DSS or the chart based algorithmic support system

· To compare the Cost effectiveness of the DSS versus the chart based algorithmic support system at the end of 12 months among hypertensive patients.

· To compare the Cost utility of the DSS versus the chart based algorithmic support system at the end of 12 months among hypertensive patients.

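### The QALY weights are given two different lower anchors, worst imaginable health and death, with no step linking them, so VAS score times time is a death-anchored QALY only if death would be rated exactly 0

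*Protocol article*

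**What the plan says.** All the relevant statements are in the protocol article, under Cost utility analysis (CUA), except the endpoint itself.

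- Health-related quality of life is measured on a "Visual Analogue Scale (VAS) preference scale with a maximum score of 100 (perfect or best imaginable health", and the other end of that scale is a "minimum score of 0 (a quality of life which equals worst health imagined".
- The next sentence lists three properties of the quality weights. The third is that they are "anchored on perfect health and death".
- QALYs are then formed directly: "The value of a health state would then be combined with the time spent to calculate the total QALYs".
- The result feeds the incremental cost-effectiveness ratio (ICER): "ICER is a ratio between the differences in the cost involved between the intervention proposed (in Indian National Rupees) and the difference in QALYs".
- Under Secondary end point, this is a named outcome: "To compare the Cost utility of the DSS versus the chart based algorithmic support system at the end of 12 months among hypertensive patients".

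The section closes by explaining why the VAS was chosen as the utility measure, so no second utility instrument is in play. The WHO BREF questionnaire appears elsewhere in the article only as a source of quality-of-life scores.

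**The concern.** A QALY needs weights on which full health is 1 and death is 0, because a year not lived counts as zero. The VAS described here has a different zero. Its floor is the worst state of living that a person can picture. The two zeros coincide only if the respondent would put death exactly at that floor. The article asserts the death anchor but describes nothing that would create it.

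The objective includes cost utility, and the abstract's Discussion says that the trial is meant to inform policy makers. A cost per QALY serves that purpose mainly by being set beside other cost-per-QALY figures. If the unit is really a year weighted from worst to best imaginable health, comparison with death-anchored figures is not like with like. The only sensitivity analysis specifically named is a change in discount rates. Over the stated one-year horizon, that would not reveal an anchoring problem.

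**Working it through.** The article states no QALY, utility or ICER value, so there is no figure to reproduce. The check is of the scale itself.

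**Inputs from the document.** The VAS runs from 0 (worst imaginable health) to 100 (best). The weights are claimed to be anchored on full health and death. QALYs are value combined with time, with no rescaling stated.

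**Inputs assumed.** d is the score that participants would give to death on the same VAS. The document does not give it, so the working uses 5 to 30, with 0 as the case where the anchors agree. The unrescaled calculation is taken to be VAS/100 times time. The article does not write this out.

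**Formulae.**

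- Unrescaled weight: V/100. Difference between arms: ΔV/100.
- Death-anchored weight: (V − d)/(100 − d). Difference between arms: ΔV/(100 − d).
- With no deaths, the anchored QALY difference divided by the unrescaled one is 100/(100 − d).
- The ICER is ΔCost/ΔQALY, so the unrescaled ICER is 100/(100 − d) times the anchored ICER.

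**Results without deaths.** The rupee column illustrates an assumed 5-point VAS gain held for one year at an assumed extra cost of Rs 1,000. The unrescaled ICER is then 1,000/0.05 = Rs 20,000.

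| d (assumed) | 100/(100 − d) | Anchored ICER (Rs) |
|---|---|---|
| 0 | 1.00 | 20,000 |
| 5 | 1.05 | 19,000 |
| 10 | 1.11 | 18,000 |
| 20 | 1.25 | 16,000 |
| 30 | 1.43 | 14,000 |

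**Direction.** A positive d means that some imaginable states are worse than death, and the unrescaled ICER is then too high. A negative d would mean that death lies below the worst imaginable health. The same formula gives 100/110 = 0.91 for d = −10 and 100/120 = 0.83 for d = −20, so the ICER would be too low. A 0–100 scale cannot record such a rating.

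**With deaths.** The factor is no longer common. Take d = 20, a 2-point VAS gain, a risk difference in death of 1% in favour of the arm with the gain, half a year lost per death and a mean VAS of 70 (all assumed):

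- Unrescaled QALY difference: 0.02 + 0.01 × 0.5 × 0.70 = 0.0235.
- Anchored QALY difference: 2/80 + 0.01 × 0.5 × 50/80 = 0.025 + 0.003125 = 0.028125.
- Ratio: 0.028125/0.0235 = 1.20, against 1.25 with no deaths.

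**The case against.** The best defence is that the two sentences describe two different things. The first gives the end-points of the raw instrument and the second the properties of the weights derived from it. A raw score and its derived weight may have different anchors, and a condensed article may leave the conversion formula to a fuller document. The article also never says outright that VAS/100 is used.

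This defence would succeed if the article showed the material for a conversion. Any rescaling needs a position for death on the VAS, and the article describes neither a rating of death nor an assumed value. It goes straight from the value of the health state to QALYs. The stated anchoring therefore has no support in the design as written, which is more than a missing detail. What stands is that the numerical error is conditional: it vanishes if d is 0 or if an unreported rescaling is applied.

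Two other points on that side also stand. First, a reader might infer that the bias runs in a known direction. The documents do not support this, because the direction depends on where death would be placed, and they do not say. Second, a reader might infer that the result could not be compared with any cost-per-QALY figure. That is too broad. Figures built on the same unanchored VAS would be comparable, and without deaths a range over d would link the result to death-anchored figures.

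**Conclusion.** The point holds as an internal contradiction about the lower anchor of the QALY weights, with a conditional numerical consequence. If VAS/100 is multiplied by time, death would be rated between 5 and 30, and nobody dies, the cost per QALY is overstated by a factor of about 1.05 to 1.43. The range for d is an assumption, and with deaths the distortion is not one common factor. The documents do not establish that the reported ratio will be wrong by any particular amount, or in any particular direction.

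The scope is narrow. Only the cost-utility secondary endpoint is touched, and there only comparison with death-anchored figures. Without deaths, a positive common factor does not change the sign of the QALY difference between arms. The systolic blood pressure endpoint and the cost-effectiveness ratio based on it are unaffected. The point should be put right before the cost-utility results are reported.

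**What to change.** Reconcile the two sentences in the cost-utility section in one of two ways.

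1. **Keep the QALY.** State the conversion (VAS − d)/(100 − d), and report the ICER over a stated range of d as a sensitivity analysis. This needs no new data. If a participant rating of being dead on the same VAS can be collected at a remaining visit, use it to inform d.
2. **Keep the raw VAS.** Delete the statement that the weights are anchored on death, and report cost per VAS-weighted year in place of cost per QALY.

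The cost is small: some extra analysis and a wider result under the first option, or a relabelled result under the second. Adding the item costs more. Some respondents may find rating death hard, and the wording would need translation and testing like the other quality-of-life material. Time is also short, since the abstract has follow-up ending in March 2013. The article schedules visits at 0, 6 and 12 months but does not say at which of them the VAS is given, so whether the item can still be added must be checked.
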